##### Sampling and Recruitment

Parents of children awaiting their pediatrician appointment will be recruited for the RCT. During this time, the RA will liaise with the intake nurse to identify families who are suitable for study participation. Families will be eligible for study inclusion if (1) children present with nonurgent medical issues, (2) children are 5 to 17 years of age, and (3) children attend their appointment with at least one parent. Parents (eg, mothers, fathers, legal guardians) will be eligible if they (1) self-identify as a child’s primary caregiver, and (2) speak and read English. The nurse will also help to differentiate urgent (eg, febrile, acute asthma attack) and nonurgent (eg, medical checkup, asthma follow-up) presentations, of which only the latter will be approached for recruitment. Families who are identified as eligible by the clinic nurse will be approached by the study RA in the waiting room of the primary care clinic. Average wait times in the Edmonton Oliver PCN are 15 to 30 minutes, so this time will be used to (1) recruit participants, (2) obtain informed, written consent (adult) and assent (child), (3) measure and input children’s anthropometric data, and (4) deliver the brief, online intervention to parents on the study-designated tablet (iPad). If families present with more than one child and both are interested in participating, only the child with the next upcoming birthday will be enrolled—this will be done to ensure that each study participant represents an independent case. As a token of appreciation and to encourage parents to complete the 1-month follow-up measure, parents will be given a Can $25 gift card to a local business (eg, grocery store).

Primary health care providers at this site have historically had around 2500 patient encounters per year [51], so our research staff will recruit families on approximately 2 days per week over several months to accumulate our study sample. Given the design of the SBIRT, parents will also need adequate time to complete everything at once (ie, saving and completing the intervention at a later date will not be possible within the SBIRT). With time constraints in mind, families will be approached to participate in the study if we—clinical/administrative staff, research team—believe parents will have sufficient time (ie, 15 to 20 minutes) to complete the intervention and research procedures while waiting for their scheduled clinical appointment. Although it is a potential barrier that some recruited parents may be unable to complete the program while they wait, previous studies have supported the feasibility of brief online interventions under similar conditions, for example, Freeborn et al [52]. Assuming 20 to 30% attrition at 1-month follow-up [53], complete data from approximately 150 parents is expected. Figure 1 represents a flow diagram of expected recruitment and retention. Based on primary care client demography, this sample size will allow us to enroll a diverse group of families that vary by age, ethnicity, family income, and weight status.

**Figure 1 figure1:**
[figure not shown]
Flow diagram of predicted progress through RCT phases (enrollment, allocation, follow-up, and analysis).

##### Data Collection

Within the GUI, we will collect the following information (see Case Report Form in Multimedia Appendix 1): families’ demographic information, children’s weight status, resources and services chosen by parents, and parents’ responses to both the intervention questions (unless allocated to the control group) and the theory-based questionnaire (see Phase I in Methods).

##### Data Management and Analysis

Security measures that adhere to provincial and federal privacy requirements will be integrated into the program. Access to the online SBIRT will be password protected, all data transactions between the Web and data services will be encrypted, and the server will be located behind a firewall to safeguard personal data.

Quantitative data analyses will be performed using SPSS version 22.0 (SPSS Inc, Chicago, IL, USA). Continuous variables will be described by univariate summaries, and frequency distributions will be determined for categorical variables. Box plots and histograms will display continuous variables, and bar charts will display categorical variables. Recruitment rate and participant characteristics (eg, sex, weight status, demographics) will be calculated to assess enrolment tendencies and biases in subgroups. Retention rate, or the proportion of participants who remain in the study at 1-month follow-up, will be calculated to assess the likelihood of attrition within and between subgroups. A bivariate statistical model (eg, Wilcoxon rank-sum test) will be used to compare program completers versus noncompleters to assess attrition bias. Hierarchical linear modeling [54] will be used to assess intra- and interlevel individual differences and group changes in the predetermined outcomes. Specifically, the primary and secondary outcomes will be assessed at the individual level (ie, nested within each intervention group) and group level (ie, between each intervention group), both at baseline and at 1-month follow-up. This form of analysis is appropriate when observations are nested within groups and/or multiple time points. Statistical significance will be set at *P*<.05.

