#### Pragmatic Trial

##### Trial Design

A parallel-group, double-blinded randomized controlled trial will be used to assess the effectiveness of the intervention. The trial has been registered publically (ClinicalTrials.gov identification number: NCT02330588) [48] and adheres to CONSORT guidelines [49]. Participants will be recruited and enrolled by an RA and RIPPLE will assign a unique, nonidentifying number to participants. The allocation sequence will be electronically generated within the GUI and to reduce the risk of selection bias, participants (n=200 parents) will be randomly assigned to one of five groups—*Eat It!* (normative), *Eat It!* (injunctive), *Move It!* (normative), *Move It!* (injunctive), or *Heads Up!* (control group). Group assignment will be done using blocked randomization—five arms, block size of five—to ensure equal group sizes—n=40/arm, equal allocation ratio of 1:1—throughout the study. To reduce the risk of performance bias, the RCT will be double-blinded. Specifically, the study-designated RA ([name]) will not be aware of participants’ intervention assignment, unless participants request assistance with the program, thus potentially revealing their assignment. Research personnel will be blinded for the remainder of the research process, including outcome assessment, in order to minimize the risk of detection bias [50]. As well, study participants will not be aware of their assignment to the intervention or control groups. Prior to the intervention, participants will receive information that is sufficient to obtain informed consent, but inadequate so as to decipher between intervention groups. Although contamination is a possibility given the close proximity of participants, given that only one participant can be recruited at a time, enrollment and recruitment will be staggered and the opportunity for participants to discuss the intervention with each other is unlikely.

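### The analysis section makes the randomised arm a nesting level; the five arms are fixed conditions, and the only nesting evident in the design is two occasions within a parent

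*Protocol article*

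**What the plan says.** Under Data Management and Analysis, the protocol article names the model: "Hierarchical linear modeling [54] will be used to assess intra- and interlevel individual differences and group changes in the predetermined outcomes". It then sets out the levels: "the primary and secondary outcomes will be assessed at the individual level (ie, nested within each intervention group) and group level". The second of these is explained as a comparison of the arms with one another, and both are to be looked at on the two measurement occasions. The reason given is "This form of analysis is appropriate when observations are nested within groups and/or multiple time points".

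The design is described elsewhere in the same article:

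- **Trial Design:** "participants (n=200 parents) will be randomly assigned to one of five groups", with "five arms, block size of five" and "n=40/arm, equal allocation ratio of 1:1". Only one participant can be recruited at a time.
- **Study Setting:** recruitment is through one primary care network.
- **Sampling and Recruitment:** one child per family is enrolled so that participants are independent. On follow-up: "Assuming 20 to 30% attrition at 1-month follow-up [53], complete data from approximately 150 parents is expected".
- **Phase I, step 3 (brief intervention):** the purpose is to compare outcomes across the five groups.
- **Study Strengths:** Phase III is to supply preliminary effect sizes for the sample size of a future cluster trial.

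**The concern.** An upper level in a hierarchical model is suited to units that are a sample from a larger population, such as clinics or schools, and whose members are correlated for reasons other than the treatment. The five arms are not such units. They are the conditions under test, chosen deliberately, and the questions concern these five only. Parents in the same arm share the treatment and, as far as the article shows, nothing else.

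The article does have real nesting, since each parent is measured twice. Its justification mentions time points, but the sentence on levels never names the parent as the unit that holds them. It names the arm.

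Following that sentence literally has one of two consequences, depending on how the arm level is used. Either the treatment comparison is judged against variation among five units, which discards most of the information from about 150 parents, or the arm effects are reported as predictions pulled towards their common mean. The second would carry straight into the planning of the next trial.

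**Working it through.** **Inputs from the protocol article.** Five arms of 40, 200 parents in all; 20 to 30% attrition; about 150 completers; significance at 0.05 (taken as two-sided). The article states no effect size, SD, power or degrees of freedom.

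**Assumptions made here.** Equal attrition, so 150/5 = 30 per arm; one outcome with SD 1; the same benefit d in all four intervention arms against control; d = 0.3, 0.5 and 0.8 SD for illustration.

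**Step 1. The article's own figures.** 5 × 40 = 200. Completers are 200 × 0.80 = 160, 200 × 0.75 = 150 and 200 × 0.70 = 140, so about 150 is the midpoint. These figures are consistent.

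**Step 2. Degrees of freedom.**

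- Arm as a fixed factor: 150 − 5 = 145 residual df; critical t = 1.98.
- Arm as upper-level unit with one active-versus-control predictor: 5 − 1 − 1 = 3 df; critical t = 3.18.
- Arm as upper-level unit with all four arm contrasts fitted: 5 − 4 − 1 = 0 df, so the arm-level variance cannot be identified.

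**Step 3. Power for the four intervention arms against control.** The standard error is √(1/120 + 1/30) = 0.204. At d = 0.5 the non-centrality is 0.5/0.204 = 2.45. From the non-central t distribution:

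| d (SD) | arm fixed, 145 df | arm as upper level, 3 df |
|---|---|---|
| 0.3 | 31% | 18% |
| 0.5 | 68% | 40% |
| 0.8 | 97% | 74% |

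The 3-df column takes its standard error from the spread of the arm means. If the model instead holds the estimated arm variance at or above zero and still refers to 3 df, simulation gives 3%, 17% and 64%, with a type I error of about 0.1%.

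**Step 4. Shrinkage, if arm effects are read as random-effect predictions.** The fraction retained is τ²/(τ² + σ²/n). With one control arm at 0 and four arms at d, the between-arm variance is τ² = d²/5.

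- d = 0.5: τ² = 0.05, and 0.05/(0.05 + 1/30) = 0.60.
- d = 0.3: τ² = 0.018, and 0.018/(0.018 + 1/30) = 0.35.
- d = 0.8: τ² = 0.128, and 0.128/(0.128 + 1/30) = 0.79.

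Those fractions treat τ² as known. When it is estimated from five arms, simulation gives an average predicted contrast of about 0.29 SD for a true 0.5 SD and about 0.12 SD for a true 0.3 SD. The arm variance is estimated as exactly zero, so that all arms appear identical, in about 13% of trials at 0.5 SD and 35% at 0.3 SD.

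Steps 3 and 4 are alternatives. The 3-df test concerns an unshrunk coefficient; the shrinkage concerns predicted arm effects. They do not both act on one estimate.

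**The case against.** The strongest reply is that the article never calls arm a random effect and gives no model equation, estimator or rule for degrees of freedom. Its reference to comparison between the intervention groups, at two time points, can be read as an ordinary fixed between-subject factor with occasions inside parents, which would be sound. A journal article commonly leaves the fixed and random parts of a model to a fuller document, which is not at hand. This stands as far as the consequences go. A reader might infer that the trial will shrink its arm effects and also test them on 3 df. The text does not support that: each consequence follows only from a particular way of fitting the model, the two concern different quantities, and some software uses approximate df.

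It is also fair that every effect size above is assumed, and that power at 0.5 SD ranges over 68%, 40% and 17% with the specification. Phase III is, moreover, described as preliminary.

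The reply does not rescue the sentence itself. This is not an omitted detail. The article states a nesting structure and offers nesting in groups as a reason for the method. The sound reading is reached only by setting that clause aside.

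**Conclusion.** The stated nesting is wrong for this design and should be corrected. That conclusion rests on the article's own description of individual randomisation, independent participants, one setting and five named arms, and it needs no assumption about effect size.

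The size of the harm is conditional on arm being fitted as the upper level. With 30 completers per arm and a 0.5 SD benefit in all four intervention arms, either power for active versus control falls from 68% to about 40% (145 to 3 df), with no df left if all four contrasts are fitted, or predicted effects average about 0.29 SD in place of 0.5 SD. The second case would mislead the planned cluster trial. If the analyst in fact enters arm as a fixed factor, neither loss occurs and the defect is one of wording.

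**What to change.** Replace the sentence on levels with: *Measurement occasions are nested within parent (random intercept). Arm, time and arm-by-time are fixed effects. Arm is not a random or nesting level. Between-arm contrasts will be reported at 1 month.* Delete nesting within groups as a reason for the method and keep repeated measurement as the reason.

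Two points need care:

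- **Use of resources and services** is described as assessed by a follow-up questionnaire. Where an outcome is measured only then, compare arms with arm as a fixed factor and no time term.
- **The concern and motivation score from the first visit** should not be adjusted for as though it preceded treatment. Phase I lists the theory-based questionnaire as step 5, after the brief intervention at step 3, and follow-up repeats that same measure. Adjusting for it, or relying on arm-by-time alone, could remove an immediate effect of the intervention. This is why the 1-month contrast is the one to report.

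The cost is analysis wording only, with no change to recruitment, data collection or conduct. A true pre-intervention score would need a new measurement and is not part of this fix.

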## Results

This is a three-phase, multi-method study designed to build, refine, and complete testing of an online SBIRT to enhance parents’ concern for, and motivation to, support children’s healthy lifestyle behaviors. Development of the project commenced in summer 2012, and the expected date of completion is fall 2016 (Table 1). The Health Research Ethics Board at the University of Alberta (Edmonton, AB) has approved this study.

**Table 1 table1:** Timeline of study-related activities.

Study activities and substeps		Year and season^a^of study															
		2012		2013				2014				2015				2016			
		S	F	W	Sp	S	F	W	Sp	S	F	W	Sp	S	F	W	Sp	S	F
**Preparatory activities**																	
	Organization of the research team	✓																	
	Ethics application		✓																
	Develop the toolbox of resources		✓	✓															
**Study activities**																	
	Phase I: Development			✓	✓	✓	✓	✓	✓	✓									
	Phase II: Refinement										✓	✓							
	Phase III: Testing												✓	✓	✓				
**Knowledge translation**																	
	Formal meetings		✓		✓		✓		✓		✓		✓		✓		✓		
	Research blog updates						✓	✓	✓	✓	✓	✓	✓	✓	✓	✓	✓	✓	✓
	Findings dissemination												✓					✓	✓

^a^Summer (S), Fall (F), Winter (W), Spring (Sp).

## Discussion

### Distinctive Features

This paper highlights the study protocol for the development, refinement, and testing of a novel SBIRT designed to enhance parents’ concern for, and motivation to, support children’s healthy lifestyle behaviors, as well as link them with relevant resources and services to help prevent childhood obesity in primary care. Historically, SBIRTs have been developed and applied to facilitate positive changes related to addictive behaviors (eg, cannabis use, problem drinking). A recent review and meta-analysis of SBIRTs for screening of alcohol consumption in primary care found that the majority of participants across 22 trials demonstrated positive behavior change (ie, reduced consumption) at 12-month follow-up [23], a finding that suggests the positive effects of this brief approach may have the potential for longevity. Furthermore, in comparison to lengthier online interventions (ie, 60 minutes or longer), positive outcomes of brief interventions were not statistically different [23], highlighting that the dosage of exposure is not necessarily proportionate to the treatment effect, thus justifying the use of a time- and resource-limited approach. In addition to the potential for positive behavior change, specific program elements unique to SBIRTs (eg, automatic screening procedures, personalized feedback, menu of resources and services) are well-suited for primary care. Although this setting prioritizes frontline prevention of chronic diseases, primary care providers report a number of barriers and challenges to fulfilling this task [13,55]. Our intervention may address this deficit and reduce the pressures and expectations faced by primary care health care providers who often lack confidence and skills in preventing childhood obesity [14]. Our SBIRT may also help families to overcome limited availability of health services for the secondary prevention of childhood obesity (eg, multidisciplinary weight management clinics, outpatient nutrition counseling). Lastly, our Web-based SBIRT for parents may enhance existing resources and health services for obesity prevention in children. For instance, the intervention may remove social barriers and provide anonymity for families that are reluctant to receive care and support in person.

Although the application of SBIRTs to the prevention of obesity in children remains untested, recent systematic reviews [11,15] have highlighted the advantages associated with online interventions (eg, family-based Internet programs, Internet counselling, Web-based interactive behavior programs) that are aligned with RIPPLE with respect to the aim of obesity prevention in children. For example, an online primary care-based program for preventing childhood obesity was well-received by clinicians and families, in which clinicians were more likely to speak with families about healthy weights, and parents intended to increase their children’s vegetable and fruit intake, postintervention [26]. It is noteworthy, however, that the majority of such interventions have focused on time- and resource-intensive models, approaches that are often difficult to implement and sustain, particularly in primary care. Additionally, given that online approaches represent a relatively new niche of study, little is known regarding the impact of online interventions on weight-related health outcomes and intentions to change lifestyle behaviors [56]. Taken together, there is a real need to develop and evaluate brief, Web-based interventions to help connect families with relevant resources and services that may *nudge* them towards healthy behavior changes in a setting where parents and children are already present and waiting.

### Study Strengths

This project was developed in direct response to health systems gaps and priority areas in Canada. To date, the research team has received strong support from health care professionals and provincial health care organization decision makers, highlighting the support for, and relevance of, our research. Second, this research will directly inform how such a brief, parent-based approach to address childhood obesity can be incorporated into everyday clinical practice in primary care. Providing families with tailored feedback, practical resources, and information on local health services will help to overcome clinical barriers associated with the primary and secondary prevention of obesity in children. Lastly, findings from this developmental study will inform a future cluster clinical trial to test effectiveness of the intervention across multiple PCN clinics. Specifically, results from Phase III of this study will (1) help to estimate preliminary effect sizes of the SBIRT, informing a sample size calculation for a future cluster RCT, (2) confirm our ability to recruit and retain participants from primary care, and (3) determine appropriateness of primary and secondary outcomes, and follow-up time points.

### Study Limitations

We acknowledge that our SBIRT is new and remains untested. Given this reality, there are a number of program components (eg, theoretical underpinnings, duration of follow-up time period) that have been informed by related projects [57,58]. Because a number of research-related parameters remain unknown, our study design includes modifying the intervention (Phase II) prior to formal testing (Phase III), which will facilitate refinement of program structure, function, language, and aesthetics before initiating testing with parents in Phase III. We also appreciate that most SBIRTs have investigated participants’ motivation to change their own individual behaviors, whereas our study assesses the motivation of parents to help change their children’s behaviors, in other words, surrogate motivation. Given this degree of separation, parents’ motivation may neither accurately reflect children’s motivation to make lifestyle behavior changes, nor be sufficient to initiate behavior change. These are relevant issues that will be explored further in follow-up research that will build on this initial study.

### Conclusions and Future Directions

Our applied health services research is timely and the objectives align with research priorities to prevent obesity in children. This protocol study encompasses the development, refinement, and testing of a parent-based, online SBIRT that will directly inform the feasibility of incorporating such an approach into everyday clinical practice. By providing families with tailored feedback and information on applicable resources and community services, our SBIRT will encourage family self-management of obesity-related behaviors in primary care. Findings from this project will confirm a number of feasibility-related parameters in the pilot study (eg, feasibility of incorporation into primary care, recruitment and retention rate, suitability of primary and secondary outcome measures) and preliminary effectiveness of the intervention, which will be tested in a future cluster RCT.

